### Objective audit of participant work samples for quality and overall transfer

A further objective audit is undertaken using an enhanced version of the Goal Instrument for Quality to determine whether principles of effective goal setting that underpin the CRM have transferred into practice following intervention. That is, the former transfer indicators ask ‘is the new practice being done, and to what extent?’ while this measure will enable exploration of the question ‘is there improvement in the quality of what is being done?’ This audit is conducted on-site by trained in-service assessors, and will allow investigation of the overall work practices of staff for evidence of changed practice. Client files will be randomly selected from three time-periods (*i*.*e*., zero to six months pre-intervention, zero to six months post-intervention, and six to twelve months post-intervention) from participants in each organisation. The care plans within files will be assessed on 17 elements of effective recovery-based goal setting by two in-service auditors. A copy of the de-identified file material is forwarded to the research team, who will also conduct the 17-point assessment of the care plan, enabling inter-rater reliability testing.

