### Participants

Participants will be randomised by work-site to either the experimental (values) or control (implementation). Cluster-randomisation will be adopted to increase the feasibility of roll out in the organisational setting (*e*.*g*., consistency across what ‘change’ for individuals within a single worksite will look like) and minimise contamination across conditions (*i*.*e*., individual randomisation would likely lead to decreased fidelity to condition due to inevitable interactions between individual staff within teams). A computerised random integer program will be used to refer worksites to condition. Once randomised, staff from within sites will be referred for training and invited to consent to participate in the research process. Blinding will not be used at the participant or worksite level for pragmatic reasons (*i*.*e*., ongoing coaching will require condition-specific protocol) and to maximise fidelity (*i*.*e*., workers will consult with colleagues from worksites in the alternate condition during the course of duties and need to understand the importance of staying within assigned protocol). Information about previous exposure to the training (*i*.*e*., staff who have participated in some CRM training before time one) will be sought to allow screening prior to inclusion in the final data set. Staff who do not consent to participation in research but are within randomised sites will still participate in all intervention components to maximise the benefit of this project for the partners, to promote intervention fidelity within the workplace, and to allow all mental health workers access to contemporary evidence-based practices and techniques.

The intervention will be facilitated by our team and comprises both training (three days) and a 12-month coaching intervention. All teams will receive the same two days of training in the CRM [10]. On the third day of training, they will receive different training activities, according to the condition (values or implementation). In-service coaches (to be trained by our team) will conduct coaching. The in-service coaches will be supported with monthly, group-based coaching-support sessions facilitated by an appropriately skilled project member. Features of each intervention condition are as follows.

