### Qualitative assessment of concordance between work samples and CRM values

A novel aspect of this research is the utilisation of a process-oriented protocol to assess worker adherence to the principles embedded within CRM. For example, the principle of personalisation (*i*.*e*., evidence of unique and person-centred approach to service delivery) is acknowledged as important in recovery [3]. Personalisation will be assessed across two dimensions (the content in the sample reflects unique expression of ideas; the language/presentation of content reflects individuality) using a three-point scale (0 = no, 1 = partially, 2 = yes). De-identified research copies of work samples are to be forwarded by participating mental health workers on a monthly basis by an on-site coordinator. Following power calculations, an online number generator will be used to facilitate random identification of an appropriate number of staff whose work-samples are to be reviewed. The samples of randomly identified staff will be reviewed using the six-point rating system at three time points (one month post-training, six months post-training, and 12 months post-training). Two trained assessors from within the research team will independently review the work samples for worker process and satisfactory inter-rater reliability will be established. We will compare observed adherence to CRM principles with the self-reported transfer and measures of autonomy obtained via the CRM-VQ (described above) at matching time periods (*i*.*e*., six and 12 months) during booster sessions to explore these differing elements of implementation.

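### The care-plan audit described as objective is scored on-site by in-service auditors who are likely to know the condition, and the stated purpose of the research team's re-scoring of copies is reliability only

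*Protocol article*

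**What the plan says.** The section on the objective audit of work samples introduces the measure with "A further objective audit is undertaken using an enhanced version of the Goal Instrument for Quality". On who scores it and where, it says "This audit is conducted on-site by trained in-service assessors", and then "The care plans within files will be assessed on 17 elements of effective recovery-based goal setting by two in-service auditors". Files come from three periods: the six months before the intervention and the first and second six months after it.

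The central step follows. Copies of the files, with identifiers taken out, are sent to the team for a second scoring, and the clause that describes this scoring reads "who will also conduct the 17-point assessment of the care plan, enabling inter-rater reliability testing". No other use of the central score is given.

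For the process ratings, the section on qualitative assessment of concordance says "Two trained assessors from within the research team will independently review the work samples". Personalisation, the worked example, is rated on two dimensions as no, partially or yes (0 to 2). Samples are taken at 1, 6 and 12 months after training, and these too are de-identified copies.

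The Participants section says of delivery "The intervention will be facilitated by our team" and of masking "Blinding will not be used at the participant or worksite level for pragmatic reasons". It also says that in-service coaches, trained and supported by the team, deliver the monthly coaching. Masking of auditors or raters is not mentioned anywhere in the article.

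**The concern.** Staff cannot be blinded in this trial and much of the outcome battery is self-report. The Data collection and handling section therefore adds objective measures of transfer, and the Data analysis section relies on work-sample audits in that role. Such a measure helps only if the scorer's expectation cannot enter the score.

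Both instruments need judgement: whether a care plan meets each of 17 quality elements, and whether its content and language are individual to the client. If scorers know the condition, a difference between the values and implementation conditions may partly reflect what they expected to find. The comparison of observed adherence with self-reported transfer and autonomy also weakens, because both sides could carry the same expectation.

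Later analysis cannot repair this. Once scores have been given without masking, no model can separate rater expectation from real quality.

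**Working it through.** No arithmetic applies, since the point is who scores what and with what knowledge. The statements are set side by side.

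**1. Could the on-site auditors know the condition?**
- The abstract and Participants section allocate condition by worksite within organisation, so knowing a file's site can be enough to know its condition.
- Blinding is ruled out at participant and worksite level. Workers are expected to consult colleagues in the other condition and to understand why they must keep to their own.
- The Anticipated challenges section adds that participants will know colleagues may be receiving different training, and that each group is given a strong rationale for its own approach.
- The auditors are in-service and work on-site.

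Knowledge of condition is therefore likely, though not stated.

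**2. Do the reasons for not blinding extend to the scorers?** The reasons given are that coaching needs a condition-specific protocol and that workers must stay within their assigned protocol. Both concern delivering and receiving the intervention. Neither prevents masked scoring of copied documents.

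**3. Does the second rating protect the outcome?** Its stated function is reliability testing. Agreement shows that raters score alike. Two raters with the same expectation can agree closely and both be wrong in the same direction.

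**4. Does the pre-intervention period protect the outcome?** Only in part. A change-from-baseline contrast would remove leniency that is constant over time at a site. Expectation of an intervention effect attaches to the files written after training, so it would not cancel.

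**5. Do the process ratings fare better?** They have two independent raters and de-identified copies, which helps. But the raters belong to the team that facilitates the training and supports the coaches. In the Implementation condition section that team states its hypothesis that the values condition will increase implementation. No masking to condition is stated, nor what de-identification removes.

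**6. Is masked scoring feasible?** Copies already go to the research team, which already applies the 17-point assessment. The Implementation condition section says both conditions work with the same protocol and practice model, so a completed document should not routinely reveal the condition. Whether a file predates training may be harder to hide, but that does not identify the condition.

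**The case against.** The strongest reply is that the article is silent on assessor masking, and silence is not a statement of unblinding. A condensed article may leave masking to the full protocol. That is right as far as it goes. A reader might infer that all raters know the condition; the text does not say so. In-service auditors are not said to come from the worksite they audit, and the two process raters are not said to deliver training themselves. What remains is what the article does fix: on-site, in-service scoring within organisations where the allocation is open.

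Three further readings go beyond the text.
- A reader might conclude that the central score is excluded from analysis. Reliability is its only stated purpose, but the article does not say which score is analysed.
- A reader might say that de-identification leaves the condition visible. The article does not say what is removed, so this is open either way.
- A reader might say that the raters come from the team that coaches. In-service coaches conduct the coaching; the team trains and supports them, and it facilitates both conditions.

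It is also fair that these audits are not the only check on self-report. The Evidence of transfer section has indicators that depend less on judgement: presence of completed LifeJET documents, days to the first one, and maintenance. The power calculation concerns the proportion transferring, not the 17-element score. This limits the reach of the point to the quality and process outcomes. It does not remove it there.

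**Conclusion.** The point stands for the two judgement-based outcomes. As written, the audit called objective is scored where knowledge of the condition is likely, the only stated purpose of the central re-scoring is reliability, and the process ratings have no stated masking. This should be changed, but it does not undermine the less judgement-dependent transfer indicators.

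The size of any bias cannot be derived from the document, and its direction is not certain, since both conditions receive a strong rationale. One might assume an SD of 2.5 to 4 for the 17-point total and a one-element shift, giving 1/4 = 0.25 to 1/2.5 = 0.40 SD, and set that beside the STARS effect of 0.25 in the team's previous study. That comparison is not supported. Both the SD and the shift are assumptions, so the result only restates them. The STARS figure is a pre-post effect on a different questionnaire.

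The verdict rests on one inference, that in-service auditors working on-site will usually know the site's condition, and on reading the stated purpose of the central rating as its only planned use.

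**What to change.** Name the research team's rating of the forwarded copies as the analysed audit outcome. Before scoring, the coordinator removes organisation, site, worker and date, replaces them with a code, and keeps the key so that site and period can be restored for the analysis. Copies from both conditions and all three periods are mixed in random order. Raters are not told the condition and, where possible, take no part in training or coach support. The on-site score is kept for feedback to the organisations and for agreement testing. The same redaction, ordering and choice of raters apply to the month 1, 6 and 12 work samples. The article should say who is masked and to what.

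The cost is clerical redaction and re-ordering of material already being collected and scored. The harder requirement is finding team raters who are unaware of the site allocation, because the team facilitates both conditions; the document does not show whether such members exist. Document content may occasionally reveal the condition. Asking raters to record a guess at the condition would show how often.

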### Qualitative assessment of concordance between work samples and CRM values

A novel aspect of this research is the utilisation of a process-oriented protocol to assess worker adherence to the principles embedded within CRM. For example, the principle of personalisation (*i*.*e*., evidence of unique and person-centred approach to service delivery) is acknowledged as important in recovery [3]. Personalisation will be assessed across two dimensions (the content in the sample reflects unique expression of ideas; the language/presentation of content reflects individuality) using a three-point scale (0 = no, 1 = partially, 2 = yes). De-identified research copies of work samples are to be forwarded by participating mental health workers on a monthly basis by an on-site coordinator. Following power calculations, an online number generator will be used to facilitate random identification of an appropriate number of staff whose work-samples are to be reviewed. The samples of randomly identified staff will be reviewed using the six-point rating system at three time points (one month post-training, six months post-training, and 12 months post-training). Two trained assessors from within the research team will independently review the work samples for worker process and satisfactory inter-rater reliability will be established. We will compare observed adherence to CRM principles with the self-reported transfer and measures of autonomy obtained via the CRM-VQ (described above) at matching time periods (*i*.*e*., six and 12 months) during booster sessions to explore these differing elements of implementation.

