### Evidence of transfer within the workplace

Transfer indicators include time to implementation and maintenance of change. Transfer indicators will replicate those used previously by the research team [51]. We will seek direct evidence of implementation of any of the specific tools with the CRM (known as LifeJET) that are used to structure and record the recovery-focused practice of mental health workers. That is, examples of completed LifeJET documents within participant files. Time to implementation is calculated by determining the number of days lapsed between the date of training and the first date an example of completed LifeJET protocols was identified for participants. Maintenance of change is calculated by determining the proportion of staff work samples that are evidencing transfer (*i*.*e*., completed examples of CRM) after 12 months in comparison to time periods shortly after training (*e*.*g*., one month, six months).

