**Figure 2 F2:**
[figure not shown]
**Diagram of the hypothesised relationships between experimental variables.** This figure illustrates direct **(A)** and meditational **(B** and **C)** relationships between experimental (e.g. autonomous motivation) and dependant variables (e.g. implementation).

We will deal with missing data using full-information-maximum-likelihood estimation (FIML). Traditional approaches to missing data (*e*.*g*., list-wise or pair-wise deletion) can lead to considerable bias in parameter estimates. In contrast FIML provides a superior approach to dealing with missing data that uses all the available information for parameter estimation [54].

Standard multiple regression analysis will test for predictors of transfer. In terms of knowledge transfer related to the new workplace practices, we will compare current findings with the pre-post effect sizes extracted from the previous work conducted by the research team [51]. In that study, effect sizes were moderate based on Cohen’s criteria (STARS = 0.25, RKI = 0.52) with a sample size of 75. Given the additional components of this intervention we are expecting slightly higher effect sizes. Data collected in the CRM-VQ will enable comparison of these predictors with participant self-reported implementation of the new work practices.

Work-sampling audits will also be used as an objective measure of transfer. We are anticipating a sample size of 200 at time point one, but have allowed for a more modest sample size of 100 in calculating power analyses. In our previous study, we found 37% of people transferred training. With this information we are able to estimate the percentage of people who need to demonstrate transferred practices in work samples in order to show a significant increase in the proportions between the former and present studies. Using Z test for proportions we have calculated that we need at least 48 out of the 100 participants to obtain a significant difference at p<0.01 to detect a 10% increase in transfer. We believe this difference is very achievable with the addition of the values-focused interventions.

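### For the work-sample concordance rating only staff are drawn at random; the samples are forwarded by unblinded workers and/or a coordinator, so selective submission is not excluded

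*Protocol article*

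**What the plan says.** The forwarding rule is in the section *Qualitative assessment of concordance between work samples and CRM values*: "De-identified research copies of work samples are to be forwarded by participating mental health workers on a monthly basis by an on-site coordinator". The sentence names two agents, workers and a coordinator, and does not separate their roles.

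The random step follows: "an online number generator will be used to facilitate random identification of an appropriate number of staff whose work-samples are to be reviewed". What is then scored is described as follows: "The samples of randomly identified staff will be reviewed using the six-point rating system at three time points", at one, six and 12 months after training. The section does not say how many samples each worker supplies or how they are chosen. On rating it says "Two trained assessors from within the research team will independently review the work samples for worker process". The result is to be compared with self-reported transfer and with autonomy from the CRM Values Questionnaire at six and 12 months.

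*Participants* states: "Blinding will not be used at the participant or worksite level for pragmatic reasons".

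Two other observed measures are collected differently. In the *Objective audit of participant work samples for quality and overall transfer*, "Client files will be randomly selected from three time-periods". In *Evidence of transfer within the workplace*, the evidence sought is "examples of completed LifeJET documents within participant files". That section also defines maintenance as a proportion of staff work samples that show transfer. *Data analysis* adds: "Work-sampling audits will also be used as an objective measure of transfer". Neither of these last two places says which stream of samples it uses.

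**The concern.** The random draw is at the level of the person, and the record is what gets rated. Drawing staff at random makes the reviewed workers representative of all workers. It does nothing to make a worker's reviewed samples representative of that worker's practice. If someone who knows the condition and knows what is being looked for decides which samples go forward, the rating may describe the better work and not the usual work. Two independent raters protect the scoring, but they see only what reaches them.

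Three things are at stake.

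- **Association with autonomy.** A more autonomously motivated worker may report higher autonomy and also take more care over what is sent. The two would then be associated without any difference in practice, even if selection is the same in both arms.
- **Arm comparison.** The values condition is meant to raise motivation, so selection could differ by arm. If it does, part of the difference in ratings is a difference in selection.
- **Level.** If forwarded samples supply the maintenance proportion or the comparison with the earlier transfer rate, equal selection in both arms would still inflate the figure.

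**Working it through.** **1. The streams side by side**

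| Stream | Source of the record | Random step |
|---|---|---|
| Concordance rating | Samples forwarded monthly by workers and/or coordinator | Staff only |
| Goal-setting quality audit | Client files | Files, from three time periods |
| LifeJET indicators | Documents within participant files | None described |
| Maintenance proportion | Staff work samples, stream not named | Not stated |
| Work-sampling audit in *Data analysis* | Not named | Not stated |

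Only the first row is tied by the text to forwarding. The maintenance comparison uses 12 months against, for example, one and six months, and the concordance samples are rated at those same points. The quality audit's six-month windows could not isolate a one-month value. Dated LifeJET documents in files could do so, since time to implementation is computed from their dates. Timing therefore does not settle the source. For the *Data analysis* sentence, the words objective, audit and work samples occur together in the heading of the quality audit, which points away from the forwarded samples if anywhere.

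**2. The plan's own figure, used here only as a yardstick**

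*Data analysis* asks for at least 48 of 100 against an earlier 37% at p<0.01. A one-sample z test gives z = (0.48 − 0.37)/√(0.37 × 0.63/100) = 0.11/0.0483 = 2.28, one-sided p = 0.011. At 49 of 100 the one-sided p is 0.0065. So 48 is reproduced to within one participant. That calculation is a separate matter and does not bear on this point.

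**3. What selection could do**

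The inputs are assumptions. A sample is scored positive or negative, samples are independent, and the true rate per sample is q = 0.37 in both arms. The 37% is borrowed from the earlier study, where it is a share of people and not of samples.

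The chance that the best of k samples is positive is 1 − (1 − q)^k.

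- k = 1: 0.370
- k = 2: 1 − 0.63² = 0.603
- k = 3: 1 − 0.63³ = 0.750

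If a share s of workers sends the better of two and the rest send a typical sample, the observed rate is f(s) = 0.37 + s × (0.603 − 0.370) = 0.37 + 0.233s.

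| Share, values arm | Share, control arm | Observed rates | Spurious difference |
|---|---|---|---|
| 50% | 50% | 0.487, 0.487 | 0 |
| 50% | 25% | 0.487, 0.428 | about 6 points |
| 75% | 25% | 0.545, 0.428 | about 12 points |
| 100% | 0% | 0.603, 0.370 | about 23 points |

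The same arithmetic applies to autonomy. If 75% of more autonomous and 25% of less autonomous workers sent the better of two, their observed rates would differ by about 12 points with identical practice.

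For the level, the share that lifts an unchanged 37% to 48% is (0.48 − 0.37)/0.233 = 0.47, or about 47% of workers. This matters only if forwarded samples feed that comparison.

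**The case against.** The strongest reply is that worker choice is not in the text. The forwarding sentence can mean that a coordinator collects and sends every sample each month, and a review of the selected workers' samples fits a review of everything in the window. This stands: selection by workers is a risk left open and not a stated procedure. A reader might infer that the rating shows what workers chose to send, but the document does not say so.

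A reader might also infer that the trial's observed transfer outcome as a whole rests on hand-picked samples. The documents do not support that. The quality audit draws client files at random and includes a pre-intervention period, and the LifeJET evidence is sought within participant files. The concordance rating asks how the work is done, while the LifeJET indicators ask whether and how much it is done.

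Third, a large arm bias needs unequal selection. Both arms receive 12 months of coaching with CRM tools and a strong rationale for their condition, and no passage points to an extreme imbalance. This also stands. The 23-point row requires everyone in one arm to select and nobody in the other.

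The last reply is that an article may leave the handling of samples to the full protocol. This stands only in part. The section already gives the randomisation tool, the unit drawn, the time points and the raters, and it puts the random step at staff level. A full protocol might add a rule for records, but the procedure as published does not protect against selection of records.

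**Conclusion.** The concern holds in a limited form. In the concordance rating, random selection stops at the worker, and the records come forward through unblinded participants and/or a coordinator, so selective submission is not excluded. The rating and its association with autonomy are exposed even if selection is equal across arms. The arm comparison is exposed only if selection differs by arm.

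The quality audit is not affected. The maintenance proportion and the comparison with 37% would be affected only if forwarded samples supply them, and the text leaves that open.

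No size can be derived from the documents. Under the assumptions above (a true 37% in both arms, binary and independent samples), a 75% against 25% split in sending the better of two gives about 12 points, and equal selection gives no arm difference. The actual rating is on a three-point scale in two dimensions, so even these figures are only a guide. It is a design weakness worth correcting because the remedy is cheap.

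**What to change.** 1. For each randomly identified worker, have the research team designate at random the record or records to be rated from that worker's files at one, six and 12 months. The on-site coordinator then copies, de-identifies and sends them. This moves the random draw to the record, as the quality audit already does for client files, and leaves the choice with neither the worker nor the unblinded site.
2. Reword the forwarding sentence so that it says who selects, who copies and who sends.
3. State which stream supplies the maintenance proportion in *Evidence of transfer within the workplace* and the work-sampling audit in *Data analysis*. If it is this one, count a drawn record without completed CRM content as not evidencing transfer in that proportion, and keep the process rating as a separate score.

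The cost is protocol wording and modest coordinator time at three time points, using a coordinator and a random file-selection procedure already in the plan. The downside is that fewer CRM-rich documents will be available to rate, and the raw transfer figures may be lower.
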